Informational component. In this component of the intervention, delivered primarily in Sessions 1 and 2, facilitators will review information about transmissibility of HIV and its association with HIV viral load and medical factors, discussion of other STIs and their effects on HIV disease, and strategies used by MSM to promote sexual health, and psychosocial problems that decrease sexual health. This component will use interactive activities to dispute myths about HIV (e.g., “Unprotected sex is not risky if you are already HIV+”) and to discuss risk which behaviours are of greater or lesser risk for HIV transmission.

Motivational component. Key to this approach is identification of areas of inconsistent or conflicting motivations. Working with participants’ own sometimes inconsistent beliefs, for example, that partners are (solely) responsible for HIV risk, but at the same time, expressing altruistic values of taking care of other gay men and contributing to gay community, offers significant starting points for carrying forward the techniques of motivational enhancement counselling. This component will be delivered primarily in sessions 2-6.

Behavioural skills component. In sessions 4-6, the facilitators will help participants manage cues that may serve as triggers for risky sexual behaviour, and to identify strategies to reduce their risk of contracting STIs and/or transmitting HIV. This component will include role-play exercises of risk-reduction skills, and will use the knowledge of the group to help individual group members to begin and maintain behavioural change.

It should be noted that although there are three different components of the intervention, the components are interlaced throughout the intervention, albeit at different amounts. For example, per motivational enhancement counselling, information provision is more appropriate at earlier stages of readiness for change53,54, and behavioural skills are more appropriate once intrinsic motivation is increased to a level in which the participant is ready to make behavioural changes.

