**4.2 Overview of the Study Design**

Written informed consent will be obtained prior to study enrolment including permission to complete study measures. Those who agree to enrol and meet inclusion criteria will be scheduled for a single assessment session to complete a demographics questionnaire, self-report measures, and a brief interview. Participants will complete 6 sessions of a small-group sexual health intervention to reduce sexual risk behaviour. Assessments will be conducted at the completion of each 6-session group, with follow-up assessments conducted at post-intervention and at 3 months following the end of each group.

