**4.4 Sample Size Estimation**

For the quantitative data analyses, to examine changes in UAI with HIV-negative or unknown serostatus partners, random coefficient regression (also known as multilevel modeling) analyses will be conducted. The random regression model employs time as a within-subjects variable, and subject-specific intercepts and slopes for the time effect (i.e., trajectories) are summarized with mean and variance parameters. The analysis has several important advantages. It accounts for serial correlation within subjects, is relatively robust to randomly missing data, and can incorporate certain non-random missing data, especially those arising from drop-outs, without biasing model estimates. Following the approach for trajectory modeling outlined by Muthén & Muthén (2002), power analyses suggest an N=40 to detect a meaningful average change (i.e., medium effect size) in UAI with =.05, and 1-=.80. Given that the groups will have 6 persons each, with 7 groups, the final sample size will be N=42.

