**4.9.3 Quantitative Measures**

The quantitative measures used in this study have been demonstrated to possess good reliability and validity, as well as documented associations with risky sexual behaviour23,51,52,59,60. It is anticipated that the entire protocol will take approximately 50 minutes to complete at each timepoint: baseline, post-intervention, and 3 months after the end of the intervention.

**Demographics Questionnaire.** Participants will complete a demographics questionnaire assessing age, ethnic/racial background, religious affiliation, educational level, living situation, marital/partner status, socioeconomic status, and sexual orientation.

**Primary Endpoint Variable: Unprotected Sexual Behaviour.** Participants will be asked to indicate their frequency of unprotected anal intercourse with HIV-negative or unknown HIV status partners in the past 3 months.

**Secondary Endpoints.** Secondary endpoints will also examine protected and unprotected 1) insertive and receptive anal intercourse with men, 2) anal and/or intercourse with women with and without a condom in the previous 3 months with partners who were HIV+, partners who were HIV-negative, and partners of unknown serostatus. Second, participants will be asked to indicate their number of HIV+ partners, HIV-negative partners, and partners of unknown serostatus in the previous 3 months. Third, participants will be asked if they had insertive or receptive anal intercourse or vaginal intercourse with their last sex partner, as well as their last partner’s serostatus.

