**4.10 Stages of the Study**

**4.10.1 Research Stage I – Study Initiation**

In Month 1, the study coordinator and 2 group facilitators from our previous Ontario HIV Treatment Network START grant on Poz Prevention will be re-hired. The project timeline can be found in Appendix 2. Both facilitators are HIV+ gay men with extensive experience with group facilitation. Through the START grant, our facilitators have been trained by [name] of the Centre for Addiction and Mental Health in motivational enhancement counselling techniques for HIV prevention. Program staff will be trained in study participant recruitment, administration of self-report measures, and data entry. Procedures for all aspects of project management will be established and implemented during the first 3 months of the project. A weekly planning meeting of staff and investigators will be initiated to begin development of project infrastructure. Staff will regularly coordinate with [name] to ensure efficiency in participant recruitment. A protocol manual will be created for conducting all aspects of the study, including detailed information on participant eligibility criteria, recruitment procedures, informed consent procedures, administration of research measures, and data management plans. Standardized project forms also will be created (e.g., protocol checklists). In addition, facilitators will be trained that if a participant experiences distress at any time, referrals for counselling will be ready at hand. Intervention program facilitators will be trained in group facilitation and will be knowledgeable about referral sources for HIV+ group members who seek information or counselling, and the project will be housed at the AIDS Committee of Toronto which has HIV-related counselling and information resources. Program delivery staff/trainees will be supervised by [name].

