**4.10.2 Research Stage II – Data Collection**

Data collection will begin in month 4 of Year 1 and will continue through month 6 of Year 2 of the study. Persons in the study who contact the study office will be informed about the opportunity to participate in the study while waiting for their appointments. Specifically, they will be told that the study is involves a series of workshops intended to improve sexual health among HIV+ MSM, that participation entails responding to several questionnaires and a brief interview at a baseline assessment taking about 120 minutes to complete, a series of 6 workshops of 90 minutes each, a post-intervention assessment of 60 minutes, and a 3-month follow-up of 120 minutes. They will also be told that $30 per hour will be provided in exchange for participation. [name] have found these recruitment procedures to be both unobtrusive and effective in other larger scale studies of HIV+ MSM.

Upon obtaining informed consent, quantitative measures will be administered in questionnaire format. Upon completion of the protocol, participants will be debriefed and given the opportunity to ask any questions. Participants will then be remunerated at $30 per hour. Qualitative interviews will explore in greater depth the evaluative questions in 4.9.2 above and also the degree to which the workshops resonated with participants’ everyday lives by asking about decision-making in recent sexual encounters.

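### The 3-month recall window at the post-intervention visit covers treatment time and, at most plausible session spacings, pre-treatment time, so the effect size should rest on the 3-month follow-up

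*Protocol*

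**What the plan says.** Section 4.9.3 defines the primary endpoint by asking men to "indicate their frequency of unprotected anal intercourse with HIV-negative or unknown HIV status partners in the past 3 months". The same section gives the battery "at each timepoint: baseline, post-intervention, and 3 months after the end of the intervention", and no other recall period is given for the middle visit.

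Section 4.2 fixes the visit times: "Assessments will be conducted at the completion of each 6-session group", with the last visit "at 3 months following the end of each group".

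Section 4.10.2 describes the intervention as "a series of 6 workshops of 90 minutes each" but gives no interval between sessions. Section 4.10.1 says "The project timeline can be found in Appendix 2"; that appendix is not among the pages at hand, so the interval may be stated there. On content, section 2.4.1 places the skills work late: "In sessions 4-6, the facilitators will help participants manage cues that may serve as triggers for risky sexual behaviour".

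For the analysis, section 4.4 says "The random regression model employs time as a within-subjects variable", with subject-specific intercepts and slopes, and a final N of 42. Section 4.10.3 allows a log10(x+1) transformation and, if that fails, a presence/absence outcome over the same 3-month window. Section 4.3 requires at least one qualifying act in the 3 months before entry.

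**The concern.** A visit held when the group ends, with a question that looks back 3 months, cannot describe behaviour after the intervention. It describes behaviour during the group and, if the group runs for less than 3 months, some behaviour before it. If baseline is taken shortly before session 1, those earlier weeks are also counted in the baseline answer.

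This matters because section 3.0 sets the trial the task of determining an effect size for a later randomised trial, and only two follow-up values exist. If the effect size were read from the baseline-to-post change, it would be too small. The trajectory could also suggest that benefit emerges only at 3 months. Section 2.2 reports that in the earlier large trial an effect seen after the course had faded 3 months later. The post-intervention visit is where that pattern would have to show, and this window blurs it.

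**Working it through.** The protocol gives no figure for this point, so there is none to reproduce beyond N = 7 × 6 = 42.

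**Inputs**
- Recall window: 3 months, taken as 91 days (13 weeks), from section 4.9.3.
- Six sessions, hence 5 intervals of *s* days, from sections 4.2 and 4.10.2. The value of *s* is an assumption.
- Lag *L* in days from session 6 to the post-intervention visit. Section 4.2 suggests 0; 7 and 14 were also tried.
- For power: N = 42, and a medium effect taken as d = 0.5 on the SD of change, two-sided 5%. The protocol gives neither a numeric effect nor sidedness, so these are assumptions.

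**1. Share of the window after the group ends** = L/91. This is 0% at L = 0, 7.7% at 7 days and 15.4% at 14 days, whatever the session spacing.

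**2. Share before session 1** = max(0, 91 − L − 5s)/91.

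| Interval | L = 0 | L = 7 | L = 14 |
|---|---|---|---|
| 3.5 days | 81% | 73% | 65% |
| 7 days | 62% | 54% | 46% |
| 10 days | 45% | 37% | 30% |
| 14 days | 23% | 15% | 8% |
| 18.2 days or more | 0% | 0% | 0% |

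At L = 0 the share exceeds one half only if s < 45.5/5 = 9.1 days, and it reaches zero at s = 91/5 = 18.2 days. The share after session 4, when skills work begins, is 2s/91: 15% if weekly, 31% if fortnightly.

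There is indirect evidence on spacing. Data collection runs from month 4 of Year 1 to month 6 of Year 2, which is 15 months. Less 3 months of follow-up, about 52 weeks remain. Seven groups run one after another would have about 7.5 weeks each, or at most about 10 days between sessions. Overlapping groups are not excluded, so this is only suggestive.

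**3. Attenuation of the baseline-to-post change** (constant act rate, L = 0). If the full effect starts at session 1, the fraction kept is 5s/91: 35/91 = 38% weekly and 70/91 = 77% fortnightly. If it builds linearly over the sessions, half of that is kept: 19% and 38%.

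**4. Power of a paired baseline-to-post test, N = 42.** Undiluted d = 0.5 gives 0.89. With the SD of change held fixed, weekly d = 0.19 gives 0.23 and fortnightly d = 0.38 gives 0.68. If baseline is taken just before session 1, the shared weeks cancel and the SD of change shrinks as well. With independent increments, d = 0.5 × √(5/13) = 0.31 (power about 50%) weekly and 0.5 × √(10/13) = 0.44 (about 79%) fortnightly.

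**5. Linear time slope over all three visits.** Take weekly sessions, visits at 0, 5 and 18 weeks, and a true step effect of 1.
- Centred times are −7.67, −2.67 and 10.33, with sum of squares 172.7.
- Undiluted values (0, 1, 1): slope × 18 = (−2.67 + 10.33)/172.7 × 18 = 0.80.
- Diluted values (0, 0.385, 1): (−1.03 + 10.33)/172.7 × 18 = 0.97.
- With time coded 0, 1, 2 the middle visit has no weight and both give 1.00.

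**6. Presence/absence fallback.** Every man scores yes at entry by eligibility, and one act before session 1 keeps him at yes. As an illustration, assume Poisson acts and that all such acts stop at session 1. With a mean of 3 per 91 days, 1 − exp(−3 × 8/13) = 84% (weekly) or 1 − exp(−3 × 3/13) = 50% (fortnightly) still score yes at the post-intervention visit. With a mean of 1 the figures are 46% and 21%.

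**7. The 3-month visit.** Its window starts when the group ends, so 0% precedes session 1 and none of it falls within treatment.

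**The case against.** The strongest reply is that the planned analysis is a trajectory over three visits, not a baseline-to-post test, and that one follow-up value is already entirely post-intervention. This stands. A reader might infer that the recall window dilutes the primary analysis as a whole, but step 5 shows that a linear slope is not reduced. What remains is a distorted trajectory shape and a weakened post-intervention contrast.

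A reader might also infer that most of the post-intervention window is untreated time. That needs sessions less than about 9 days apart with the visit on the day of session 6, and the text at hand states neither. At fortnightly spacing 77% of the window falls after session 1.

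The drop in power from 0.89 to 0.23 is likewise not a property of this trial. It applies to a contrast that the protocol does not name, at an assumed weekly spacing, with the SD of change held fixed.

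A constant window also has merit: it matches the eligibility criterion and keeps the visits comparable. Replacing it at the middle visit with acts since the first session would clash with section 4.10.3. Under the presence/absence outcome, a shorter window would by itself lower the proportion reporting any act and could create a false benefit.

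Finally, an analysis plan not shown here could name the visit that carries the effect size. That is possible, but the recall window and the visit time are fixed in the protocol, and they make the middle value unsuitable for that role.

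**Conclusion.** The point holds in a limited form. With the visit at completion of the group, none of its recall window follows the finished intervention, or at most 15% with a 2-week lag. Some of it precedes session 1 at any interval under about 18 days: 62% if weekly and 23% if fortnightly, with no lag. The baseline-to-post change keeps 38% or 77% of an immediate effect, and less if the effect builds over the sessions. The presence/absence fallback is the more fragile version, since a single early act hides a complete change.

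The documents do not support a claim that the window is mostly pre-treatment, or that the overall slope is biased toward zero. The percentages rest on an assumed session interval and a constant act rate. Severity is moderate: this is a single-arm Phase II study with one clean follow-up value already planned.

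**What to change.** State in sections 4.4 and 4.9.3 that the primary contrast and the reported effect size are baseline versus the 3-month follow-up. Their windows have equal length and neither overlaps treatment, provided baseline is completed before session 1. Label the post-intervention value secondary, and say that its window includes treatment and possibly pre-treatment time. State the session interval and the permitted lag between session 6 and the post-intervention visit.

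Keep the 3-month item at the post-intervention visit for comparability. Optionally add a separate item on acts since session 1, with the number of days recorded. Analyse it only as a secondary rate, and do not mix it into the log10(x+1) or presence/absence analysis.

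The cost is a few sentences and, if wanted, one extra question. The downside is that the primary contrast then rests on a single visit with more exposure to dropout. Under the assumption d = 0.5 on the SD of change, a two-sided paired t test needs 34 complete pairs for 80% power, so 42 enrolled allows for 8 losses (8/42 = 19%). The optional item must be in place before data collection, because acts recorded without dates cannot be separated later.

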**Potential Theoretical Mediators.** Per the IMB model, Information, Motivation, and Behavioural Skills will be assessed to examine the relative effects of each component on UAI with non-HIV+ partners. The HIV-Knowledge Questionnaire-1876 will be used to assess knowledge of basic HIV information. Questions will also ask about knowledge of very recent data, such as the PHAC’s statement on the Swiss Cohort Study77, and knowledge of criminalization of unprotected sex for HIV+ individuals (CITES). Participants’ motivations to perform 8 risk-reduction actions will be assessed per recent research assessing the IMB model60. Examples of items include intentions to keep condoms nearby, to use a condom with a new sexual partner, and to use a condom when drunk or high on a substance. Self-efficacy for behavioural skills in risk reduction will be assessed using a 6-item measure60. Items include “I am certain I can use a condom with my main sex partner.” Participants will also be asked about whether they have engaged in 5 risk reduction behavioural skills over the past month, such as refusing to have unsafe sex and guiding sex toward safer sex behaviour.

**Additional Measures.** Due to data implicating substance use in unprotected intercourse among MSM**38**.**78-81**, participants will indicate how many times they have been intoxicated when drinking alcohol or used an injection or non-injection substance in the past 3 months. To assess for possible confounding due to social desirability reporting bias on sensitive behaviours such as sexual behaviour and drug use, participants will complete the Marlowe Crowne Social Desirability Scale - Short Form81. If any of these variables is associated with unprotected sexual behaviour, they will be examined as potential other mediators in analyses examining the effect of the intervention on unprotected anal intercourse with HIV-negative or unknown HIV status partners. CD4 count and viral load will be requested through self-report for the present study. These measures will serve as medical indices of severity of HIV illness in our HIV+ sample.

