**4.11 Research Stage IV: Disseminate Findings,Write Proposal for RCT**

After a thorough assessment of the strengths and weaknesses of the proposed intervention, together with feedback from stakeholder communities, a manual describing the intervention as set within a consultative model will be developed and work will begin on the development of a proposal for delivery and testing of the modified intervention in Toronto and other smaller sites. The training resources and findings from this project will enter into the larger Ontario Gay Men’s HIV Prevention Strategy.

A key problem with many interventions created through research is the lack of consultation with community agencies that will actually administer the intervention upon completion of research activities75. Thus, in the final phase, the research team and the rest of the Poz Prevention Working Group will return with results to stakeholder communities for discussion on how to integrate the future RCT into community work, and organize results to present to community forums, policy makers, the Ontario AIDS Network, the Ontario HIV Treatment Network and the Canadian Association of HIV Research conferences, and potentially international conferences. With consultation with agencies that will help to deliver the intervention, the primary investigators will then refine the intervention manual to reflect the way the intervention was delivered in the present study. The team will then design and implement a RCT to test the efficacy of the intervention in Toronto and other smaller sites throughout Canada. The intervention evaluated in this Phase II design can be compared to both treatment-as-usual and social cognitive theory-based interventions that were efficacious among general samples of PHAs but that do not specifically address barebacking among MSM48,49.

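### One arm in which every man is offered information, motivation and skills together can show associations with UAI, not the relative effects that the protocol sets out to examine

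*Protocol*

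**What the plan says.** Under the sub-heading on potential theoretical mediators, Protocol Section 4.9.3 states that "Information, Motivation, and Behavioural Skills will be assessed to examine the relative effects of each component on UAI with non-HIV+ partners". It then lists the measures: a knowledge questionnaire with added questions, intentions for 8 risk-reduction actions, a 6-item self-efficacy scale, and a question on "whether they have engaged in 5 risk reduction behavioural skills over the past month". The same section asks about UAI with HIV-negative or unknown-status partners over the past 3 months, and sets three assessments: baseline, post-intervention and 3 months after the end of the intervention.

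Section 2.4.1 uses the same three names for the content of the sessions and says that "the components are interlaced throughout the intervention, albeit at different amounts". Information falls mainly in sessions 1 and 2. Of the motivational part it says "This component will be delivered primarily in sessions 2-6", and of the skills part "In sessions 4-6, the facilitators will help participants manage cues that may serve as triggers for risky sexual behaviour".

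Section 4.2 describes one course for everyone: "Participants will complete 6 sessions of a small-group sexual health intervention to reduce sexual risk behaviour". Section 4.4 gives 7 groups of 6, N=42. Comparators are left to a later randomised trial (Section 4.11): "The intervention evaluated in this Phase II design can be compared to both treatment-as-usual and social cognitive theory-based interventions".

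**The concern.** The sentence in Section 4.9.3 announces an inference (effects) and a comparison (relative). The design has no contrast that could support either. No man is assigned to one element without the others, none is assigned to nothing, and no construct is set by the investigators independently of the other two.

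At stake is how the result will be read. Sections 4.9.1 and 4.9.2 say that monitoring results feed into improving the intervention, and Section 4.11 plans a revised manual and a randomised trial of the modified programme. If three coefficients are reported as relative effects, a chance or confounded difference between them could be taken as evidence for expanding or cutting content.

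Timing is a second, conditional issue. If skills used and UAI are compared at the same visit, most of the UAI period comes before the period in which the skills were reported.

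**Working it through.** **1. Is there a contrast?** The argument can be checked under both meanings of *component*.

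- *Delivered content.* Information is mainly in sessions 1–2, motivation in 2–6 and skills in 4–6. The skills sessions lie wholly inside the motivational ones, and every group follows the same course. Attendance is recorded (Section 4.9.2) but not randomised, so men who missed particular sessions are not a valid comparison. No component effect is identifiable.
- *Measured construct.* Scores differ between men and over time, so an association with UAI can be estimated. Reading it as an effect needs two links. Without a control group, change in a score cannot be attributed to the intervention. The link from score to UAI is not randomised, and all three constructs are targeted together. Section 4.3 also admits only men with recent UAI, so some fall in UAI would be expected from regression to the mean alone.

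Under either meaning, what remains is association.

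**2. Precision of one association.** Inputs: N=42 (Section 4.4), all men with complete data (assumed), r = 0.30 (assumed for illustration).

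- Fisher z = atanh(0.30) = 0.310; SE = 1/√(42−3) = 0.160.
- 0.310 ± 1.96 × 0.160 gives −0.004 to 0.623.
- Transformed back, the 95% CI is −0.004 to 0.553, about 0.00 to 0.55.
- The correlation detectable with 80% power at two-sided 5% is tanh((1.96+0.84)/√39) ≈ 0.42.

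**3. Precision of a comparison between constructs.** The protocol gives no correlations between the measures, so a range is shown. Assume three equally correlated measures (correlation ρ) and R² = 0.20. The standard error of the difference between two standardised coefficients is √[2(1−R²)/((n−4)(1−ρ))]. For n=42 and ρ=0 this is √(1.6/38) = 0.205.

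| ρ (assumed) | SE of difference | Difference detectable with 80% power | Power if true difference is 0.3 |
|---|---|---|---|
| 0 | 0.205 | 0.57 | 31% |
| 0.3 | 0.245 | 0.69 | 23% |
| 0.5 | 0.290 | 0.81 | 18% |
| 0.7 | 0.375 | 1.05 | 12% |

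The protocol's N=40, rounded up to 42 = 7 × 6, was set for the average change in UAI (Section 4.4). It states no power for the mediators, so there is no figure to reproduce here.

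**4. Recall windows, if analysed at the same visit.** The skills-behaviour window is 1 month and the UAI window is 3 months, both ending at the visit. The overlap is 1/3, so 2/3 of the UAI period precedes the skills period.

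At the post-intervention visit the UAI window may also reach back before session 1. Session spacing is not stated. Take 13 weeks for 3 months, five gaps between six sessions, and the assessment at the last session (all assumed):

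- weekly sessions: 13 − 5 = 8 of 13 weeks (62%) fall before session 1;
- fortnightly sessions: 13 − 10 = 3 of 13 weeks (23%);
- gaps of 13/5 = 2.6 weeks or more: none.

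**5. The lagged pairing.** The UAI window at the 3-month follow-up starts at about the post-intervention visit. Relating post-intervention scores to follow-up UAI is therefore the one pairing in which the changed score precedes the outcome period.

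**The case against.** The best defence is that the sentence is about questionnaires. It stands under a mediator heading, refers to the IMB model and is followed by a list of scales, so *component* most naturally means the measured construct. That is right, and it disposes of one tempting reading: that the protocol claims to separate the effects of session content. The text does not clearly make that claim. The defence does not rescue the word *effects*, because associations between unrandomised scores and UAI in one arm remain associations.

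Three further objections stand and limit the point.

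- A reader might infer that the protocol commits to a same-visit analysis. It does not say so, and the planned visits already allow a lag. Choosing the model could be left to a statistical analysis plan, although no such plan can supply a contrast that the design lacks.
- A reader might take the one-month window to apply to all skills measurement. It applies only to the five skills behaviours. The self-efficacy, knowledge and intention measures have no stated recall window.
- A reader might infer that mediator coefficients alone would reshape the manual. The protocol combines questionnaire, interview and facilitator data with stakeholder feedback, calls the mediators potential, announces no formal ranking, and acknowledges the small sample and Phase II purpose (Section 4.9.2).

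**Conclusion.** The point holds as a mismatch between a stated inference and the design. Relative effects of information, motivation and skills on UAI cannot be identified here under either meaning of *component*; exploratory associations can be estimated. This conclusion rests on the described design alone and needs no assumed figure.

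The size is illustrative. An association of 0.30 would be compatible with anything from about 0.00 to 0.55. With R² = 0.20 and correlations of 0 to 0.7 among the measures, a true difference of 0.3 between two coefficients would be detected only 31% to 12% of the time. Loss to follow-up would make both worse.

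The timing problem is conditional on a same-visit analysis, is confined to the five skills behaviours as far as the one-month window goes, and depends on unstated session spacing for any reach back before session 1.

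The primary endpoint, its analysis and the sample size are not affected. The correction is worth making because it is cheap and the results are meant to inform the next trial.

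**What to change.** In Section 4.9.3, replace the aim of examining the components' relative effects with: *exploratory association of baseline to post-intervention change in information, motivation and behavioural skills with UAI at the 3-month follow-up, adjusted for baseline UAI*. Report each association with its confidence interval, and state that no ranking of, or causal claim about, components will be made.

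One detail needs care. Section 4.10.3 allows UAI to be dichotomised as present or absent. Since entry requires recent UAI (Section 4.3), a dichotomised baseline would be nearly constant and adjustment for it would do little. The baseline covariate should therefore be the reported frequency, transformed if needed.

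The change needs no new visits, measures or participants. The downside is a weaker claim, and the lag does not remove confounding; it only puts the scores before the outcome period.
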